**Discussion:**

The HARPOON study will provide relevant information on the efficacy and safety of prophylactic haloperidol treatment for in-hospital delirium and its effects on relevant clinical outcomes in elderly at-risk medical and surgical patients.

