## Background

Delirium is a serious and frequently occurring complication of (acute) illness in older hospitalised patients with prevalence rates of more than 30%
[1]. Delirium is a neuropsychiatric syndrome characterised by a disturbance of consciousness which has an acute onset and fluctuating course, typically developing within hours and lasting for several days to weeks or even months
[1-3].

In older patients, development of in-hospital delirium is associated with a range of negative patient outcomes such as increased hospital length-of-stay, long-term cognitive- and functional decline, new institutionalisation, and increased mortality
[4-6], thereby also leading to substantial healthcare costs
[7]. Because of the associated healthcare and economic burden, multicomponent non-pharmacological intervention strategies targeting delirium risk factors in the hospital setting have been introduced. Although they are effective in reducing delirium incidence in elderly general medicine and surgical patients
[8,9], their effectiveness seems largely to depend on protocol adherence
[10] which may be low due to high staff workload. In addition, non-pharmacological multicomponent hospital-based interventions do not seem to affect post-discharge outcomes such as cognitive or functional status, and nursing home placement
[11]. Low-dose haloperidol prophylaxis has been shown to lower delirium incidence in older postoperative intensive care unit (ICU) patients
[12,13], and duration and severity in (mainly elective) hip-surgery patients
[14]. However, the effect of haloperidol prophylaxis on in-hospital delirium development and post-discharge outcomes in an older general medicine and surgical patient population has not been studied yet.

This paper describes the design of the multicenter, randomised, double-blind, placebo-controlled clinical trial to evaluate the efficacy and safety of early prophylactic treatment with low dose haloperidol on in-hospital delirium, and post-discharge outcomes in acutely admitted older medical and surgical patients.

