#### Secondary outcome measures

Severity and duration of delirium; number of delirium-free days; hospital length-of-stay; adverse events; all-cause mortality in-hospital and within six months post-discharge; cognitive and physical function at baseline, three, and six months post-discharge; new institutionalisation post-discharge; number of hospital admissions within six months post-discharge.

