With respect to delirium, the VMS program based standardised hospital care covers identification and modulation of precipitating delirium risk factors such as medication reviews and orientation and noise-reduction measures, creating an optimal background regimen for conduction of this trial in all participating hospitals. Patients who positively confirm one or more of the VMS delirium risk questions (VMS ≥1) are considered at-risk for developing delirium during hospital admission. Patients with VMS 0 on first evaluation are not eligible for this study. Eligible patients will be asked for informed consent. In case of inability to write, patients must provide verbal consent in the presence of an independent witness (preferably patients’ proxy) who may then sign the informed consent form. The study medication, haloperidol 1 mg or identical placebo tablets, will be given orally to participants twice daily at 12 pm and 8 pm for a maximum of seven consecutive days (14 treatment dosages) on top of standardised care based on the implemented VMS program ‘Vulnerable elderly’. During the seven-day intervention period nursing staff will screen participants for delirium symptoms. Additionally, a trained observer (physician or geriatric nurse) will daily visit participants to detect the presence of delirium, register potential adverse events based on 24-hour nursing observations, clinical judgement, and electrocardiogram (ECG) monitoring, and to check for adherence to standardised adequate environmental manipulations for delirium such as orientation measures. For patients who have not developed delirium within seven days of initiation of the study intervention, daily assessment stops. Patients who develop delirium are evaluated daily by the observer to record delirium severity and duration until symptoms diminish. Study drug administration is terminated early if a participant develops delirium, is transferred to a non-participating care unit such as the ICU, refuses further participation in the trial, the QTc interval is more than 500 milliseconds (ms), is discharged from the hospital, or dies within seven-day of initiation of the study intervention. In case of established delirium or if the assigned study intervention is thought to have a direct influence on the patient’s treatment, the treating physician will request for unblinding and may further decide on treatment. For unblinding of treatment assignment, the treating physician is able to contact the VUmc consultant pharmacist through a central telephone number 24 hours a day, seven days a week.

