[30]. An ECG is performed at baseline, after two and six treatment dosages, and at the end of the intervention period to register QTc intervals. ECG is repeated daily until a steady state is reached in case of prolonged QTc interval (more than 450 ms and 460 ms, for men and women respectively), or if the patient is taking other QT prolonging medications. On study inclusion, and at the time of ECG after study drug administration dose six, a 4 ml blood sample is collected, and plasma is stored at -80°C at the VUmc Clinical Pharmaceutical and Toxicological Laboratory to determine haloperidol levels. On discharge, the number of days spent in the hospital is recorded.

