### Statistics

For the data analysis IBM SPSS Statistics 20 will be used. Clinical trial data will be primarily registered in paper case report forms and later transcribed into the electronic data capture system of OpenClinica, open source clinical trail software. The primary analysis is aimed at evaluation of the primary outcome of this study: the incidence of in-hospital delirium according to the DSM-IV criteria in older at-risk patients aged 70 years or over who are acutely admitted through the ED for a general medicine or surgical specialty within seven days of initiation of the study intervention. Data from all randomised patients will be analysed according to the Intention-to-treat principal. The primary outcome delirium incidence is considered a binary outcome, present or absent. Patients who for example leave the hospital (or die in-hospital) within seven days of start of the study intervention without experiencing delirium will be regarded negative on the primary outcome. Patients who do not complete the intervention will be monitored during their in-hospital stay for occurrence of delirium. The number of patients diagnosed with delirium at least once in the seven days following initiation of the study intervention will be calculated for both the haloperidol and placebo group, and subsequently this number is divided by the total amount of patients assigned to the matching group, reflecting in-hospital delirium incidence ratio within seven days of initiation of the study intervention. Pearson’s chi-squared test will be used to compare this number between the two groups. Continuous normally distributed data including patient demographic data will be tested with Student’s *t* test. The Mann–Whitney *U* test is used for comparison of non-normal distributed data such as secondary outcome measures concerning efficacy of prophylactic haloperidol treatment. Log rank test will be used to establish the time to (first) delirium diagnosis (number of delirium-free days), which will be compared between groups. Adverse events in both groups will be globally described. Kaplan-Meier estimates will be used to display survival probability within 6 months after hospital discharge for patients with and without diagnosed in-hospital delirium.

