[14]. Aforementioned study results suggest that although a three times daily dosing strategy with haloperidol seems superior in reducing symptom severity in the treatment of established delirium, it is not efficacious in reducing the incidence of postoperative delirium when administered prophylactic. Since the primary objective of this study is to investigate the effect of prophylactic haloperidol administration on delirium incidence in a broader elderly patient population, a different treatment regimen of 1 mg haloperidol or placebo twice-daily for a maximum intervention period of seven consecutive days was chosen. In case of established delirium, symptoms tend to fluctuate during the course of the day with potential evening or night-time worsening. Given that haloperidol peak plasma concentrations occur within two to six hours after oral administration, administration of the prophylactic study intervention in the early afternoon and mid evening was favoured. Capsule count of returned study medication in addition to evaluation of nurse medication charts confirmed by plasma drug levels is used as a reliable method of assessing study medication adherence in this clinical trial
[35].

In addition to extrapyramidal side effects, more rare side effects as ventricular arrhythmia’s and TdP are a great concern for physicians initiating haloperidol treatment in a patient. To date, there are no consensus practice guidelines on QT(c) monitoring for the prevention of TdP in the hospital setting, and recommendations are primarily based on clinical experience
[36-38]. During this study routine ECG measurements will be performed and plasma haloperidol levels will be determined to evaluate individual QTc changes related to these haloperidol levels in order to expand the current knowledge base.

Eligibility criteria include that a subject has the cognitive capacity to understand the scope of the study and is able to provide informed consent independently. Based on the sample size calculation, a large numbers of subjects must be screened. Therefore, a brief and valid screening instrument was selected to assess cognitive function (6-CIT)
[24,25] on admission in a face-to-face interview. The Dutch version of the 6-CIT has high diagnostic accuracy compared with the cognitive impairment criterion standard Mini-Mental State Examination

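### Safety is a stated aim, but no between-arm estimate with an interval is specified for adverse events or QTc, although both are recorded in both randomised arms

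*Protocol article*

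**What the plan says.** **Aim and outcomes.** The Background describes a "placebo-controlled clinical trial to evaluate the efficacy and safety of early prophylactic treatment with low dose haloperidol on in-hospital delirium". The Abstract's discussion paragraph promises information on the "efficacy and safety of prophylactic haloperidol treatment for in-hospital delirium". The list of secondary outcomes includes "number of delirium-free days; hospital length-of-stay; adverse events; all-cause mortality in-hospital and within six months post-discharge".

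**Collection.** Under Study design, a trained observer visits daily to "register potential adverse events based on 24-hour nursing observations, clinical judgement, and electrocardiogram (ECG) monitoring". Under Data collection, "An ECG is performed at baseline, after two and six treatment dosages, and at the end of the intervention period to register QTc intervals". Neither sentence is limited to one arm, and the Randomisation section says that observers are blinded to assignment. Blood for haloperidol level is drawn at inclusion and once after dosing, with the ECG after dose six.

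**Analysis.** The Statistics section names a chi-squared test for the delirium count, a t test for normally distributed continuous data, a Mann-Whitney test for non-normal data (with efficacy secondary outcomes as the example) and a log rank test for time to delirium. On safety it says: "Adverse events in both groups will be globally described". The Discussion gives the purpose of the ECGs and plasma levels as "to evaluate individual QTc changes related to these haloperidol levels in order to expand the current knowledge base".

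**The concern.** The adverse-event sentence states a method, and it stands next to comparative methods for the efficacy outcomes. A description by group gives counts without a measure of how far the arms could truly differ. At about 195 patients per arm, a small number of events is then easily read as evidence of safety.

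For QTc, the stated analysis does not use the strength of the design. Placebo patients should have no haloperidol level, so the relation of QTc change to level is informed mainly by variation within the active arm. That variation is not randomised, and patient factors that alter the level may also alter QTc. The comparison of assigned arms avoids this confounding and uses ECGs that are already scheduled.

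At stake is how well the trial can support the safety half of its aim. The primary result is not affected.

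**Working it through.** **1. What is specified, side by side**

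| Outcome | Recorded in both arms? | Stated analysis | Between-arm estimate with interval? |
|---|---|---|---|
| Adverse events | Yes, daily (Study design) | Description in both groups (Statistics) | None specified |
| QTc | Yes, baseline and repeatedly (Data collection) | Individual change against plasma level (Discussion) | None specified |

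Only one scheduled post-dose ECG, the one after dose six, has a matching plasma sample. The ECGs after dose two and at the end of the intervention have none, so the level analysis also leaves some of the QTc data unused.

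**2. Number per arm.** The article gives no figure for safety. The only figure that enters is 195 per arm from the sample size section. It reproduces for 20% v 10%, two-sided 5%, 80% power: the unpooled formula gives 196.2 (197 per arm), the pooled formula 199, and the power at 195 is 79.2%. So 195 is used below.

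**3. Event proportions** (counts and rates are assumptions, since the article gives none)

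- Assumed 6/195 = 3.1% v 2/195 = 1.0%. The difference is 2.1 points. Wilson limits are 1.42% to 6.55% and 0.28% to 3.66%. Newcombe 95% CI:
  - lower: 2.05 - sqrt((3.08 - 1.42)² + (3.66 - 1.03)²) = -1.1
  - upper: 2.05 + sqrt((6.55 - 3.08)² + (1.03 - 0.28)²) = 5.6
- Zero events in one arm: the upper limit of the exact two-sided 95% interval is 1 - 0.025^(1/195) = 1.9%.
- Half-width of a 95% CI for a risk difference, 1.96 × sqrt(2p(1 - p)/195), at a common rate p: 2.0 points at 1%, 4.3 at 5%, 6.0 at 10%, 7.9 at 20%.

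**4. QTc** (SD and baseline correlation r are assumptions; complete data)

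Half-width = 1.96 × SD × sqrt(1 - r²) × sqrt(2/195), with sqrt(2/195) = 0.1013.

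| SD (ms) | r = 0 | r = 0.5 | r = 0.7 |
|---|---|---|---|
| 25 | 4.96 | 4.30 | 3.54 |
| 30 | 5.95 | 5.16 | 4.25 |

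Over a wider assumed SD of 20 to 40 ms, the unadjusted half-width is 4.0 to 7.9 ms.

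**5. Effect of missing ECGs.** With m patients per arm contributing, each half-width grows by sqrt(195/m). If only 100 per arm had an ECG at a given time (an assumption), the factor is sqrt(1.95) = 1.40, and 4.96 ms becomes 6.9 ms. Under Study design, study drug stops at delirium, transfer to a non-participating unit, refusal, QTc above 500 ms, discharge or death. The two mid-treatment ECGs are scheduled by dose count, so later ECGs come from a smaller and selected group. The ECG after two doses is the least affected.

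**The case against.** **The placebo comparison is already made.** A reader might infer from the Statistics sentence that the randomised comparison goes unused for safety. The documents do not support that. The sentence covers both groups, which implies a display by arm. The Data Safety Monitoring Board section adds review of unblinded results every six months, evaluation of mortality by arm at each death, and a mortality interim analysis after 125 patients per arm have completed. This part of the objection stands. However, the by-arm review that is spelled out there concerns mortality and serves monitoring; it specifies no final estimate for extrapyramidal effects, arrhythmia or QTc.

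**QTc has other uses.** A reader might also infer that relating QTc to drug level is the only use of the ECGs. That is too strong. ECG monitoring feeds adverse-event registration, QTc above 500 ms ends study drug, and prolonged QTc triggers repeat ECGs. The general t test sentence could cover QTc, although it does not name it. What remains is narrower: the one analysis of QTc values that the article describes is against drug level.

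**This is detail for the analysis plan.** The Statistics section names no confidence interval for any outcome, the primary included, and an unseen plan may say more. This is the strongest objection and it lowers the weight of the point. It does not remove it, because the article states a method for adverse events and a purpose for the QTc data, and both are weaker than the data allow.

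**A between-arm QTc estimate is not automatically unbiased.** Correct for the later ECGs, because stopping is linked to delirium, discharge and QTc itself. The fix therefore centres on the early ECG.

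**Rare events cannot be compared usefully.** Also correct; the 1.9% limit with zero events shows it. Counts with exact limits are enough there.

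**Conclusion.** The point holds as a cheap improvement. Safety is an aim and adverse events are a secondary outcome, but the stated method is a global description in both groups, and the stated analysis of QTc values is a non-randomised relation to plasma level. No between-arm estimate with an interval is specified for either.

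At the planned size such estimates would be informative for common events (half-width about 4 to 8 points at assumed rates of 5% to 20%) and for mean QTc (about 4 to 8 ms unadjusted at an assumed SD of 20 to 40 ms). They would be weak for rare events such as Torsade de Pointes. All these figures rest on assumed event rates, SDs and correlations and on complete data; early stopping would widen the QTc intervals. Sample size, alpha and the primary analysis are unaffected.

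**What to change.** Replace the adverse-event sentence in the Statistics section with text along these lines:

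- *For each class of adverse event (for example extrapyramidal effects, ventricular arrhythmia or Torsade de Pointes, QTc above 500 ms), the number of patients with at least one event will be given by assigned arm, with the risk difference and 95% CI. These are estimates, not tests. Very rare events will be given as counts with exact limits.*
- *Post-dose QTc will be compared between assigned arms in a model adjusted for baseline QTc, with the difference and 95% CI. The ECG after two doses is the main time point, because later ECGs are affected by stopping of study drug. The number of patients with data will be reported by arm at each time.*
- *The relation between haloperidol level and QTc change is exploratory.*

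The event classes should be defined before unblinding; the article mentions these three but does not define them as endpoints.

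Cost: a few sentences and a little more analysis, with no new data. The downside is several safety estimates without multiplicity control and wide intervals for rare events, which the report should say plainly.

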## Discussion

This stratified randomised, placebo-controlled, double-blind clinical trial studies the efficacy and safety of haloperidol prophylaxis for prevention of delirium in older at-risk patients aged 70 years or over who are acutely admitted to the hospital through the ED for general medicine or surgical specialties, because generalisability of existing study results from well-designed RCTs in this field are limited to postoperative (mainly elective) hip-surgery
[14] and ICU patients
[13].

In general, in-hospital delirium occurs within three or four days after admission or surgery
[12,31], but the mean time to onset may vary up to approximately six days in ICU patients
[13]. Because delirium severity and duration amongst other things were chosen as secondary outcome parameters, a study intervention-period was selected that is long enough to also identify delirium developing under prophylactic haloperidol treatment. Treatment response after initiation of haloperidol treatment is to be expected within 24 to 48 hours after initiation of therapy
[32,33]. A small RCT in 47 hip surgery patients aged 70 and older demonstrated that a haloperidol treatment regimen of 1 mg three times daily was more effective in reducing severity of established delirium than 1.5 mg twice-daily or 3 mg once-daily (mean highest DRS-R-98 score ± standard deviation of 15.8 ± 5.2, versus 21.3 ± 4.7, and 19.2 ± 6.1 respectively), while duration of delirium tended to be shorter in the twice-daily dosing group (2.3 ± 1.8 days, versus 3.9 ± 2.6 and 4.1 ± 1.9 days in the three times daily and once-daily group respectively). No side effects were noted in the total study population (total haloperidol dose 3 mg/day)
[34]. In a large placebo-controlled RCT in 430 hip surgery patients aged 70 years and older, a three times daily prophylactic regimen with haloperidol (total dose 1.5 mg/day, maximum intervention period six days) did not significantly reduce postoperative delirium incidence in hip surgery patients, though it did significantly reduce delirium severity (mean highest DRS-R-98 score 14.4 ± 3.4 versus 18.4 ± 4.3) and duration (5.4 versus 11.8 days, 95% CI = 2.0-5.8; p < 0.001) in the haloperidol compared to the placebo group respectively
[14]. Aforementioned study results suggest that although a three times daily dosing strategy with haloperidol seems superior in reducing symptom severity in the treatment of established delirium, it is not efficacious in reducing the incidence of postoperative delirium when administered prophylactic. Since the primary objective of this study is to investigate the effect of prophylactic haloperidol administration on delirium incidence in a broader elderly patient population, a different treatment regimen of 1 mg haloperidol or placebo twice-daily for a maximum intervention period of seven consecutive days was chosen. In case of established delirium, symptoms tend to fluctuate during the course of the day with potential evening or night-time worsening. Given that haloperidol peak plasma concentrations occur within two to six hours after oral administration, administration of the prophylactic study intervention in the early afternoon and mid evening was favoured. Capsule count of returned study medication in addition to evaluation of nurse medication charts confirmed by plasma drug levels is used as a reliable method of assessing study medication adherence in this clinical trial
[35].

In addition to extrapyramidal side effects, more rare side effects as ventricular arrhythmia’s and TdP are a great concern for physicians initiating haloperidol treatment in a patient. To date, there are no consensus practice guidelines on QT(c) monitoring for the prevention of TdP in the hospital setting, and recommendations are primarily based on clinical experience
[36-38]. During this study routine ECG measurements will be performed and plasma haloperidol levels will be determined to evaluate individual QTc changes related to these haloperidol levels in order to expand the current knowledge base.

Eligibility criteria include that a subject has the cognitive capacity to understand the scope of the study and is able to provide informed consent independently. Based on the sample size calculation, a large numbers of subjects must be screened. Therefore, a brief and valid screening instrument was selected to assess cognitive function (6-CIT)
[24,25] on admission in a face-to-face interview. The Dutch version of the 6-CIT has high diagnostic accuracy compared with the cognitive impairment criterion standard Mini-Mental State Examination
[23]. Although the 6-CIT has not been validated for telephone administration, we considered it to be accurate for use over the telephone given that it includes diagnostic properties (e.g. temporal orientation, and object recall) similar to a six-item screener suitable for telephone administration
[39]. The Katz ADL has been shown a reliable way to collect data on ADL by telephone
[40]. Telephone follow-up was chosen because it is safe and more efficient than re-inviting subjects for a face-to-face interview.

In conclusion, the HARPOON study is a well-designed double-blind, placebo-controlled RCT that we believe will provide relevant information on the efficacy and safety of early administration of low-dose haloperidol for preventing delirium in at-risk elderly patients in the hospital setting, and its effects on post discharge outcomes. The predicted study completion is May 1^st^ 2015.

